### Adverse events and safety

All adverse events (AE) will be collected. The recording and follow-up of AEs will be made from the time when study treatment is started until the end of study treatment. Serious AEs will be followed up until resolved or the event stabilises.

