Subjects eligible for inclusion in the study have to fulfil all of the following criteria: Signed informed consent and expected cooperation of the patients for the treatment and follow-up must be obtained and documented according to ICH GCP, and national/local regulations before trial activities are begun. Must be willing and capable of taking the study drugs and meet for tests and follow-up as described. Diagnosed type 1 diabetes (E10.9) within 100 days. First injection of insulin maximum 100 days prior to screening. If aged 36–45 years, a current insulin regimen of both basal and prandial insulin or alternatively use of an insulin pump should exist. Aged 18–45 years old. Presence of antibodies at clinical practice or at screening to at least one of the following antigens: insulin/IAA, GAD-65, IA-2 and ZnT8. Remaining stimulated peak C–peptide ≥0.20 nmol/L. If age 36–45 years, peak C-peptide should be <2.0 nmol/L. Effective contraceptive methods throughout the study.	Subjects fulfilling any of the following criteria are not eligible for inclusion in this study: Contraindications to ixekizumab. Treatment with any oral or injected glucose-lowering agents other than insulin. A history of haemolytic anaemia or significantly abnormal haematology/coagulation results at screening. Participation in other clinical trials with a new chemical entity within the previous 3 months. Subjects with severe obesity (BMI >35 kg/m^2^ if age 18–35 years and BMI >30 kg/m^2^ if age 36–45 years). Subjects with other autoimmune diseases, for example, Mb Crohn, Ulcerative colitis, Graves' disease, psoriasis, psoriatic arthritis and axial spondylarthritis, except coeliac disease and hypothyroidism, which do not need to be excluded. Active serious or chronic infections (ie, in case the patient had a serious infection (eg, pneumonia, cellulitis), has been hospitalised, has received intravenous antibiotics for an infection within 12 weeks prior to screening visit, had a serious bone or joint infection within 24 weeks before screening visit, has ever had an infection of an artificial joint. Known immunodeficiency or patient is immunocompromised to an extent that participation in the study would pose an unacceptable risk to the patient. Active or latent tuberculosis. HIV or active hepatitis B or C. Active or recurrent fungal infection. Subjects with myocardial infarction, stroke, unstable angina or heart failure in the last 6 months. Current clinically significant cardiac arrhythmias as verified by ECG. Planned surgery during the treatment period of the study (except minor surgery on skin lesions, eg, nevus). For female subjects: Positive pregnancy test, presently breast-feeding or unwillingness to use effective contraceptive measures for the duration of the study and 3 months after discontinuation. For male subjects: intent to procreate during the duration of the study or within 3 months after discontinuation or unwillingness of their partner to use effective contraceptive measures for the duration of the study and 4 months after discontinuation. Any history of malignancy in the last 5 years except for completely resected squamous or basal cell carcinoma of the skin. Administration of live attenuated vaccine(s) (LAV) within 2 months of enrolment. Or intended use of LAV during the treatment period. The investigator judges that the clinical diagnosis of type 1 diabetes set is incorrect or uncertain (needs to be confirmed by discussion with experienced diabetologist if excluding due to this criterion) Allergy against ingredients of the investigational products. Known allergy or hypersensitivity to any biologic therapy (active substance or excipients) that would pose an unacceptable risk to the patient if participating in the study. Presence of serious disease or condition, which in the opinion of the investigator makes the patient non-eligible for the study. Liver injury criteria: patients with active hepatobiliary diseases or at screening having alanine aminotransferase (ALT) or aspartate aminotransferase (AST) >2.5 times the upper limit of normal (>2.5 x ULN). Laboratory abnormalities at screening: Neutrophil count <1500 cells/μL (=1,5 *10^9^ cells/ L) Platelet count <100 000 cells/μL (= 100 *10^9^ cells/ L) Haemoglobin <8.5 g/dL (= <85 g/L) (males) and <8 g/dL (= <80 g/L) (women)

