### Dose and administration

Ixekizumab/placebo will be administered by the participant via subcutaneous (sc.) injections for a total treatment period of 12 months. Two sc. injections (160 mg) will be administered at week 0, one dose (80 mg) at week 2, 4, 6, 8, 10 and 12 and continue with a maintenance dose (80 mg) every fourth week for a total treatment period of 12 months. The same dosing schedule is used for treatment of psoriasis.

The syringes for ixekizumab and placebo will have a similar look and not be possible to distinguish. Each syringe will contain 1 mL solution of ixekizumab or placebo. The syringes containing ixekizumab will deliver 80 mg of ixekizumab.

Ixekizumab and placebo will be provided by Eli Lilly and Company through their investigator-initiated trials program.

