### Dropouts

Participants who drop out from the study will be asked for a follow-up on an additional visit and the following blood samples will be checked: HbA1c, C-peptide and proinsulin. Insulin doses and concomitant medications will be recorded. The dropouts will not be replaced.

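### Adverse-event recording ends with study treatment, so new events after treatment are not captured, and the rule for participants who stop early is unclear

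*Protocol article*

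**What the plan says.** All places are in the protocol article.

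- **Adverse events and safety** fixes both ends of the window: "The recording and follow-up of AEs will be made from the time when study treatment is started until the end of study treatment". One sentence extends it: "Serious AEs will be followed up until resolved or the event stabilises".
- **Table 2** marks adverse events at visits 3 to 9 (baseline, weeks 2, 4, 13, 26, 39 and 52). The marks carry no condition on still taking study drug. The row is empty for weeks 104 and 208.
- **Dropouts** provides one additional visit with HbA1c, C-peptide and proinsulin, and adds: "Insulin doses and concomitant medications will be recorded". Adverse events are not listed.
- **Statistical analysis** defines the safety population as everyone with at least one dose.
- **Table 1** has criteria that reach past the end of treatment. Women are excluded for "unwillingness to use effective contraceptive measures for the duration of the study and 3 months after discontinuation". Men are excluded for "intent to procreate during the duration of the study or within 3 months after discontinuation" or for "unwillingness of their partner to use effective contraceptive measures for the duration of the study and 4 months after discontinuation".
- **Dose and administration** says that, after week 12, participants "continue with a maintenance dose (80 mg) every fourth week for a total treatment period of 12 months". It does not name the week of the last dose.

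**The concern.** The cut-off is stated outright, so the article's condensed form does not explain it. Two problems follow.

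First, an event that begins after treatment ends has no route into the safety record, whether serious or not. The sentence on serious events governs how long an event is followed. It does not open a period for recording new ones.

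Second, the phrase about the end of study treatment can mean a participant's own last dose or the end of the planned 12 months. Under the first meaning an early stopper drops out of recording while staying in the safety denominator. Under the second, recording continues for as long as the participant attends. Sites could apply either.

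At stake is whether the safety comparison covers equal observation time. If participants stop at different times in the two arms, simple proportions with an event would compare unequal periods. The protocol uses no data monitoring committee and plans no interim analysis, so the recorded adverse events carry much of the safety evaluation.

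**Working it through.** The article gives no figure for the length of the adverse-event window, so there is none to reproduce. The one related figure, the dropout allowance, does reproduce: 114 / (1 − 0.10) = 126.7, rounded up to 127, which leaves 127 − 114 = 13 expected dropouts.

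**Step 1: who is covered, by passage**

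| Situation | Adverse events and safety, read literally | Table 2 | Dropouts |
|---|---|---|---|
| On drug, attending | recorded | recorded to week 52 | not applicable |
| Stopped drug, still attending | not recorded after stopping | recorded to week 52 | not applicable |
| Left the study | not recorded after stopping | no visits | visit lists no enquiry |
| New event after the treatment period | not recorded | no mark | not applicable |

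The second row is a contradiction. The third and fourth rows are gaps in the text as it stands.

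**Step 2: completers**

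Inputs and assumptions:
- Doses fall at weeks 0, 2, 4, 6, 8, 10 and 12, then every 4 weeks from week 16 (Dose and administration). The last dose is not stated; week 48 and week 52 are both taken as assumptions.
- Recording is taken to run to the week 52 visit (Table 2).
- The illustrative window is 3 months after the last dose, borrowed from Table 1: 3 × 52/12 = 13 weeks.

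Unrecorded weeks = last dose + 13 − 52. Total weeks = last dose + 13.

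- Last dose at week 48: 48 + 13 = 61; 61 − 52 = 9; 9/61 = 15%.
- Last dose at week 52: 52 + 13 = 65; 65 − 52 = 13; 13/65 = 20%.

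With the 4-month period that Table 1 sets for partners of male participants (4 × 52/12 = 17.3 weeks), the unrecorded time is 13.3 weeks (last dose at week 48) to 17.3 weeks (last dose at week 52).

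**Step 3: early stoppers, literal reading only**

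Unrecorded weeks before week 52 = 52 − week of stopping.

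- Stop at week 13: 39 of 52.
- Stop at week 26: 26 of 52.
- Stop at week 39: 13 of 52.

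For scale, suppose all 13 expected dropouts stop treatment when they leave and do so uniformly over the year (an assumption). The mean loss is then 26 weeks: 13 × 26 = 338 of 127 × 52 = 6604 planned participant-weeks, or 5%. This excludes any time after week 52.

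**The case against.** The strongest case on the other side has five parts.

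- **The end of treatment may be a trial-level date.** The article speaks of a total treatment period of 12 months, and Table 2 marks adverse events unconditionally to week 52. A participant who stops injections but keeps attending may well be recorded. This stands. A reader might infer that every early stopper leaves the safety record on the day of stopping, but the text supports that only on its literal reading. The 39-week figure is therefore an upper bound.
- **The contraception rule is an eligibility criterion.** A reader might infer that the plan regards participants as exposed for 3 months after stopping. It does not say so, it gives no half-life, and it uses 4 months for partners of male participants. This stands. The 3 months serve here only to give the gap a scale.
- **The dropout visit may include an enquiry in the full protocol.** The article also says that all adverse events are collected. This weakens the point if the silence is taken alone. It does not remove it, because the stated cut-off would exclude new events at that visit on the literal reading.
- **Bias by arm is hypothetical.** A reader might infer that events in the active arm will be undercounted. No stopping rates by arm are given, and the 13 dropouts are an all-cause allowance across both arms. Unequal observation time is a possibility only.
- **The concern about faster disease is largely met elsewhere.** The Discussion raises a possible acceleration of type 1 diabetes. The dropout visit and weeks 104 and 208 measure C-peptide, HbA1c and insulin doses, which would show it. The empty adverse-event row at weeks 104 and 208 therefore gives no ground for collecting serious events there; those visits also lie far outside a window of a few months. Exposure-adjusted rates are a matter for the analysis plan, which is not shown.

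None of this supplies a provision for recording new events after treatment ends.

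**Conclusion.** The point holds in a limited form. As written, new adverse events that begin after the end of study treatment are not captured, and the follow-up of serious events does not change that. For early stoppers, the safety section, Table 2 and the safety-population definition do not fit together and must be reconciled.

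The completers' gap of 15% to 20% rests on two assumptions: the week of the last dose, and the borrowed 3-month window. The early stopper's loss of up to 39 of 52 weeks also needs the literal reading and a stop at week 13. The primary endpoint is not affected. The change should be made, because the safety comparison is incomplete by rule and the remedy is simple.

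**What to change.** Amend the safety section in three ways:

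1. Record AEs and SAEs through week 52 for every participant who received a dose, whether or not study drug has been discontinued. This brings the text into line with Table 2 and the safety population.
2. Add an AE/SAE enquiry to the existing dropout visit.
3. Add one short AE/SAE contact after the last dose, for example by telephone, with the length of the window chosen and justified by the sponsor.

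The cost is a short amendment, one contact per participant and a small site workload. Inclusion began in September 2022 and the last randomisation was anticipated for May 2025, so on that schedule treatment runs to about May 2026. Participants already past the chosen window will lack the late contact. That shortfall depends on calendar time and applies equally to both blinded arms, but it should be reported. Treatment, blinding, randomisation and the primary analysis stay as they are.

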### Lab, monitoring and study drug delivery

The majority of blood samples, including C-peptide levels measured during the MMTT as for the primary endpoint, will be analysed at a central laboratory at the Karolinska University Hospital Laboratory. In brief, centrally analysed blood samples include islet cell autoantibodies, safety blood samples (including renal and liver function), viruses (HIV and hepatitis), thyroid function and coeliac biomarkers.

Only blood samples that require rapid analysis due to transport sensitivity will be handled locally; this includes glycated haemoglobin (HbA1c). The effect on HbA1c is a secondary endpoint and, therefore, must be standardised as much as possible. To ensure consistency, the same laboratory method will be used. In Sweden, all HbA1c methods are calibrated against a central standardisation system via EQUALIS, ensuring comparable HbA1c levels. At the local site, a chest X-ray will also be performed to screen for active/latent tuberculosis.

Biobank samples in whole blood, serum and plasma for all participants will be collected, and in a subsample of participants, also peripheral mononuclear cells.

Each study site will be monitored before the start of the trial, repeatedly during the study and at the end of the trial. Gothia forum, Gothenburg, Sweden, will monitor the trial. No data monitoring committee is used in this study since it is relatively small, short in duration and involves a medication already approved for other indications (eg, psoriasis).

Eli Lilly and Company provides study medication and Tamro AB handles study treatment logistics.

### Statistical analysis

The full analysis set (FAS-population) consists of all participants who receive at least one dose of study medication and have at least one follow-up measurement.

The per-protocol population (PP-population) consists of all participants in the full analyses set without any significant protocol deviations. The PP-population is defined at the clean file meeting before the database is locked.

The safety population consists of all participants who received at least one dose of study medication.

The primary efficacy variable, difference in change from baseline to week 52 in residual insulin secretion measured by stimulated C-peptide 2 hour area under the curve profile measured by MMTT, will be estimated by ANCOVA adjusting for differences between treatment groups in stimulated C-peptide 2 hour area under the curve at baseline. The secondary efficacy variables (difference in change in insulin need, time in glucose range, time in hypoglycaemia and HbA1c) will also be estimated by ANCOVA adjusting for difference in the evaluated variable at baseline. No interim analyses are planned in the study.

Regarding continuous exploratory variables, the difference between the two groups for normally distributed variables will be analysed using ANCOVA adjusting for baseline value and for not normally distributed variables using Fisher’s non-parametric permutation test. Dichotomous variables will be analysed using Fisher’s exact test and ordered categorical variables using Mantel-Haenszel Chi-square trend test. Statistiska Konsultgruppen, Gothenburg, Sweden, has been consulted for statistical methods.

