### Study visits

The visit schedule will be as follows: randomisation, week 2, 4, 13, 26, 39 and 52. MMTT will be performed at randomisation, week 4, 26 and 52. At all visits, physical examinations will be performed and HbA1c collected. Blood pressure and weight will be taken at all visits except week 2. A detailed description of the trial procedures is provided in table 2. Additionally, participants will complete a series of questionnaires evaluating intervention treatment satisfaction, well-being, hypoglycaemia confidence, diabetes-related distress and physical activity at the study site:

Diabetes Treatment Satisfaction Questionnaire (DTSQ) is an 8-item scale measuring aspects of satisfaction scored on a 7-point Likert scale, including domains of current treatment satisfaction, convenience of treatment, understanding of diabetes, recommendation of treatment and continuation of treatment. Two versions will be used: the DTSQs and DTSQc. DTSQs is used to record current treatment satisfaction throughout the trial and the DTSQc is used to retrospectively compare the treatment arms at week 52.^16^

**Table 2 T2:** Trial procedures

	Patient info (two visits)	Screening visit (fasting*)	Baseline randomisation (fasting)	Week 2 Follow-up±1 week	Week 4 Follow-up±10 days (fasting)	Week 13 Follow-up±2 weeks	Week 26 Follow-up±2 weeks (fasting)	Week 39 Follow-up±2 weeks	Week 52 Follow-up±2 weeks (fasting)		Weeks 104 and 208 Extension phase (±3 months) (fasting)	
Variables	Visit 1	Visit 2	Visit 3	Visit 4	Visit 5	Visit 6	Visit 7	Visit 8	Visit 9		Visit 10+11	
Information visit	X											
Obtain informed consent	X											
Inclusion/exclusion criteria		X										
ECG		X										
Demographics		X										
Length		X										
Medical history		X	X						X			
Date of diagnosis of type 1 diabetes and first insulin injection		X										
Smoking status			X									
Family history of type 1 diabetes		X										
Concomitant medication		X	X	X	X	X	X	X	X			
Physical examination		X	X	X	X	X	X	X	X			
Blood pressure			X		X	X	X	X	X			
Weight		X	X		X	X	X	X	X			
Information regarding type of glucose monitoring			X			X	X	X	X		X	
GAD, ZnT8, insulin/IAA and IA-2-antibodies		X							X			
Mixed Meal Tolerance Test		X	X		X		X		X		X	
HbA1c		X	X		X	X	X	X	X		X	
Proinsulin			X						X			
Hematology†		X	X		X		X		X			
Clinical Chemistry‡		X	X		X		X		X			
Urine pregnancy test		X										
HIV, hepatitis serology, IgA transglutaminase, thyroid status		X										

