Tuberculosis screening (QuantiFERON and chest X-ray)		X										
Liver status§		X	X		X		X		X			
Downloading CGM data from Libre Pro iQ		*	X			X	X		**	X	***	X (2 visits)
Sampling for biobank			X		X		X		X			
Types of insulin and doses of insulin			X		X		X		X		X	
Questionnaries¶			X				X		X			
Adverse events			X	X	X	X	X	X	X			

*During this visit, Libre Pro iQ will be initiated to collect masked CGM data.

**CGM will be initiated 4 weeks preceding this visit and the data collected at week 52.

***CGM will be initiated at week 104 and 208 and the data will be collected at a separate visit.

* Blood samples will be taken in a fasting state.

† Hb, MCV, WBC, platelets, absolute counts of neutrophils (segmented), lymphocytes, monocytes, eosinophils, basophils.

‡ Na, K, Ca, CRP, Creatinine.

§ 3AST, ALT, Alkaline phosphatase, Bilirubin (total and direct).

¶ DTSQs, WHO-5, SWE-HCS, SWE-PAID-20 and IPAQ (at Week 52, DTSQc is included).

World Health Organization-5 (WHO-5) is a 5-item scale that assesses patient well-being.^17^The hypoglycaemia confidence questionnaire is a 9-item scale that evaluates patient confidence regarding their ability to prevent and address hypoglycaemic events.^18^Problem Areas in Diabetes Scale, Swedish version (SWE-PAID) is a 20-item scale which assesses worries and concerns specifically related to diabetes and its management. It has been shown to be a good marker of diabetes-related distress.^19^International Physical Activity Questionnaire (IPAQ) is a 7-item scale that assesses minutes spent in light, moderate and vigorous physical activity per week. Scores are expressed as energy expenditure in estimated metabolic equivalent task minutes.^20^

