### Endpoints

The primary endpoint will be the change in residual insulin secretion measured by stimulated C-peptide 2-hour area under the curve profile measured by MMTT between baseline and week 52. The secondary endpoints are insulin need (U/kg), time in glucose range (3.9–10 mmol/L), time in hypoglycaemia (<3.9 mmol/L) and HbA1c. Exploratory variables include glycaemic variability, well-being, hypoglycaemia confidence, treatment satisfaction and diabetes-related distress. All predefined endpoints are shown in box 1.

Box 1Predefined endpointsPrimary endpointChange in residual insulin secretion measured by stimulated C-peptide 2 hour area under the curve profile measured by mixed meal tolerance test (MMTT) between baseline and week 52.Secondary endpointsChange in mean Insulin dosage per kilo body weight for 24 hours from baseline to week 52.Change in time with glucose levels in range (3.9-10 mmol/l) measured by masked CGM (Libre Pro iQ) from baseline to week 52.Change in time with hypoglycaemia (<3.9 mmol/l) measured by masked CGM (Libre Pro iQ) from baseline to week 52.Difference in HbA1c from baseline to week 52.Exploratory endpointsChange in time in hypoglycaemia (<3.0 mmol/l) measured by masked CGM (Libre Pro iQ) from baseline to week 52.Change in proinsulin/c-peptide ratio in serum as a measure of beta cell stress from baseline to week 52.Change in time in target (3.9-8 mmol/l) measured by masked CGM (Libre Pro iQ) from baseline to week 52.Change in time in hyperglycaemia >10 mmol/l and >13.9 mmol/l measured by masked CGM (Libre Pro iQ) from baseline to week 52.Change in glycaemic variability measured by SD, CV and MAGE by masked CGM (Libre Pro iQ) from baseline to week 52.Change in proportion of patients with peak residual insulin secretion measured by MMTT: stimulated C-peptide >0.4 nmol/mL from baseline to week 52.Change in WHO-5 scores from baseline to week 52.Change in DTSQs scores from baseline to week 52.Change in DTSQc scores estimated at week 52.Change in HCS scores from baseline to week 52.Change in PAID scores from baseline to week 52.Change in IPAQ scores from baseline to week 52.The same variables described above regarding primary, secondary and exploratory endpoints will be evaluated if the variable is measured at a specific time point from baseline to week 4, baseline to week 13 as well as baseline to week 26.

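### Non-normal exploratory variables are given a permutation test without the baseline adjustment that normal ones receive, and DTSQc has no baseline for the stated ANCOVA (minor)

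*Protocol article*

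**What the plan says.** The Statistical analysis section of the protocol article sets two rules for continuous exploratory variables. The between-group difference "for normally distributed variables will be analysed using ANCOVA adjusting for baseline value and for not normally distributed variables using" Fisher's test, described as a "non-parametric permutation test". No covariate is named for that second branch. The secondary variables have no such switch: they "will also be estimated by ANCOVA adjusting for difference in the evaluated variable at baseline". The primary variable is likewise analysed by ANCOVA on its baseline.

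Box 1 in the Endpoints section defines nearly all the continuous exploratory endpoints as changes, for example "Change in glycaemic variability measured by SD, CV and MAGE by masked CGM (Libre Pro iQ) from baseline to week 52". A two-group permutation test would therefore naturally be run on change scores.

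DTSQc differs. Box 1 lists it as "Change in DTSQc scores estimated at week 52". The Study visits section says "the DTSQc is used to retrospectively compare the treatment arms at week 52", and the questionnaire footnote to Table 2 adds "at Week 52, DTSQc is included". DTSQs, by contrast, is scheduled at baseline, week 26 and week 52.

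**The concern.** Two matters arise from the same paragraph.

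First, the baseline adjustment depends on the shape of the distribution, although skewness is no reason to give it up. A permutation test can be run on baseline-adjusted values as easily as on raw changes. A variable sent to the permutation branch is analysed with less precision than the same data allow. It also has weaker protection against a chance baseline imbalance, because a change score corrects for baseline with a fixed coefficient of 1 and not an estimated one. Time below 3.9 mmol/L, a secondary endpoint, always has the adjustment. Time below 3.0 mmol/L, exploratory and from the same sensor data, would lose it if judged non-normal.

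Second, the rule for normally distributed variables cannot be applied to DTSQc, which has no baseline value.

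At stake are the precision of some exploratory results and a clear analysis line for one questionnaire.

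**Working it through.** **The plan's own figures.** The only sample size in the article is for C-peptide: difference 0.18, SD 0.34 nmol/L, two-sided 5%, power above 80%. Per arm, n = 2 × (1.960 + 0.842)² × (0.34/0.18)² = 56.01, rounded up to 57, so 114 in total. The exact t-test power at 57 per arm is 80.0%. With 10% dropout, 114/0.9 = 126.7, so 127. Both stated numbers reproduce (1:1 allocation assumed, as the article gives no ratio). No power is stated for any exploratory endpoint; 57 per arm is used below only as a realistic size.

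**Precision of change score against ANCOVA.** Let the SD be σ at both times and the baseline to week-52 correlation be rho.
- Variance per participant of the change: 2σ²(1 − rho).
- Residual variance after adjusting for baseline: σ²(1 − rho²).
- Ratio, ANCOVA over change: (1 − rho²) / [2(1 − rho)] = (1 + rho)/2.
- Factor on the required N for the change score: 2/(1 + rho).
- Power of the change-score test where ANCOVA has 80%: Φ(2.802 × √[(1 + rho)/2] − 1.960).

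The article gives no rho, so a range is shown.

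| rho | (1+rho)/2 | N factor | Power, change score | Loss from 80% |
|---|---|---|---|---|
| 0.3 | 0.65 | 1.54 | 62% | 18 points |
| 0.5 | 0.75 | 1.33 | 68% | 12 points |
| 0.7 | 0.85 | 1.18 | 73% | 7 points |
| 0.8 | 0.90 | 1.11 | 76% | 4 points |
| 0.9 | 0.95 | 1.05 | 78% | 2 points |

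**Skewed data, additive effect.** Simulation with lognormal outcomes (log SD 0.8), 57 per arm, 1,500 trials and 499 permutations, with the effect set so that ANCOVA has about 80% power. At rho 0.3, 0.5, 0.7 and 0.85, the permutation test on change scores had power 65%, 71%, 78% and 78%. The permutation test on residuals from a regression of the week-52 value on baseline had 82%, 82%, 85% and 82%. Type I error was 4.7% to 5.7% for ANCOVA and for both permutation tests.

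**Skewed data, proportional effect.** Lognormal outcomes (log SD 0.7), 30% reduction, 57 per arm, rho on the log scale. At rho 0.3, 0.5, 0.7, 0.8 and 0.9, power was 41%, 51%, 73%, 85% and 98% on change scores, against 67%, 74%, 88%, 95% and 99.8% on baseline-adjusted residuals. Type I error was 4.1% to 5.8%. The loss is larger here, 26 points at rho 0.3 and 15 at rho 0.7, and falls to about 2 at rho 0.9. The log SD and the effect are assumptions.

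**DTSQc.** No arithmetic applies. The rule needs a baseline value; Box 1, the Study visits text and the Table 2 footnote all place this questionnaire at week 52 only. The two cannot be combined as written.

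**The case against.** The strongest reply is about scope. The switch touches exploratory variables only, none of them with a power target, and the primary and secondary analyses keep ANCOVA throughout. That stands, and it sets the severity.

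It can also be said that a test on change already uses the baseline. That stands too: the change score is valid and only less efficient, and at a correlation of 0.8 or 0.9 the loss is small.

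A third reply is that the plain permutation test is exact, while permuting residuals is only approximate, so there is a trade-off. This does not stand for the form proposed here. Residuals from a model with baseline alone, without treatment, do not change under the sharp null when treatment labels are permuted, so the test keeps its validity.

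On DTSQc, the intent to compare arms on the week-52 score is plain, and the permutation branch needs no baseline. That makes it a wording gap and not a threat to the result, but the ANCOVA rule still cannot be applied to it.

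A reader might infer more than the text supports:
- That the method is chosen after seeing the outcome data. The article does not say when or how normality is judged; that may be in the SAP and may be done blinded.
- That estimates would not be comparable across endpoints. Under randomisation, the difference in mean change and the ANCOVA coefficient target the same mean difference; they differ in precision.
- That particular variables will lose the adjustment. Which ones prove non-normal is not stated.

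**Conclusion.** The point holds as a minor one. The article states a rule that names no baseline adjustment for non-normal continuous exploratory variables, and a standard two-group Fisher permutation test has none. On change scores the cost is a factor of 2/(1+rho) on the required N, from 1.54 at rho 0.3 to 1.05 at rho 0.9, assuming equal variances. It would be tempting to say that much of the power is lost. The documents do not establish this: the size depends on a correlation, a degree of skew and an effect that they do not give, and the loss runs from about 2 to 18 points under the formula. The test remains valid.

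The DTSQc point needs no assumption: the questionnaire has no baseline, so the ANCOVA branch cannot be used for it. No primary or secondary conclusion depends on either matter.

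**What to change.** State that every continuous exploratory variable with a baseline is baseline-adjusted. Where normality is doubtful, keep the permutation test but apply it to residuals from a regression of the week-52 value on baseline, permuting the treatment labels; equivalently, report the ANCOVA estimate with a permutation p-value. Give DTSQc its own line: compare the week-52 score between arms, for example with baseline DTSQs as the covariate. If the SAP already says this, no change is needed beyond checking that it agrees with the article.

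The cost is a few sentences in the SAP and a few lines of code. No extra data are needed, since the baselines, including DTSQs, are already collected.
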